### The program

#### Program theory

OVK is based on Beck's Cognitive Theory [35-37], the ABC-model of Ellis [38], and the Cognitive Theory of Seligman [39]. On the basis of their experiences, people consciously and unconsciously construct their own cognitive schemes by which they organize and process ideas and thoughts, feelings and experiences about the world, the future, other people and themselves [40]. The way people perceive the world and interpret their experiences depends upon the kind of cognitive schemes they have internalized. During a specific event, the cognitive scheme is activated, triggering an automatic thought that elicit a feeling. These automatic thoughts can either be positive, negative or neutral. In turn, these thoughts and feelings influence the way people behave, and the behavior displayed evokes certain consequences [40]. In CBT clients become aware of the link between thoughts, feelings and behavior, they learn to question the validity of automatic thoughts, to change negative automatic thoughts into more positive and realistic ones, to change their behavior, to cope with their problems, and to improve self-regulation [40].

#### Program content and structure

OVK consists of 16 lessons of 50 minutes. The first 8 lessons are devoted to explaining and practicing the CBT derived principles. Lessons 9 to 16 are directed at social and coping skills, self-esteem, problem solving, and decision making. During every lesson, the theory behind the techniques is shortly explained followed by actively practicing the skills by students. Several means are used for teaching, such as discussions, role-plays, and skits. Group leaders are responsible for group atmosphere and cohesion, and they will guide discussions and role-plays. Each lesson includes homework for the next lesson. Practicing skills facilitates internalization of these skills, which results in better program effects [23].

In lesson 1 to 8, students are familiarized with the CBT-principles; the relation between an event, thought, feeling, and behavior. First, students are introduced to the program, whereby building group cohesion, discussing confidentiality, and setting group rules are central. The students are told they will learn to deal with daily situations they feel or think pessimistically about. Afterwards, the link between a situation, thought, feeling and behavior is outlined. Inaccurate negative automatic thoughts (also called 'mind traps') are discussed. Challenging mind traps by means of formulating alternative realistic-optimistic thoughts on the spot, and searching for proof of your thoughts, is practiced. Lessons 9 to 16 are devoted to interpersonal problem-solving whereby the CBT-principles taught in the first half of the program are applied to the interpersonal domain. In sum, students learn about: (1) The link between situations, thoughts, feelings, and behaviors, 2) cognitive biases, including pessimistic versus optimistic explanatory styles, 3) cognitive restructuring skills, and 4) students learn a variety of techniques for coping and problem-solving, including assertiveness, negotiation, decision making, and relaxation.

#### Program delivery

The program will span approximately 5 months. Classes will be split up in two groups, thus consisting of 12-15 students, because this appeared to be the ideal class size for teaching PRP [28]. Gender constellation of the groups might differ. Previous research on all girl or co-ed groups does not show substantial differential effects of PRP on depressive symptoms as a function of gender constellation [41]. The 10 group leaders will have an MSc degree in clinical psychology or pedagogy. They will be trained during a 5-day workshop by two experienced psychologists of the Radboud University, who are both experts in Cognitive Behavioral Therapy. We will organize a group supervision session twice during the course of the program. Individual supervision will consist of frequent contact by phone and email to enable group leaders to feel supported, and to receive help when needed. Group leaders rate their adherence to the program content every lesson by completing a short questionnaire. The 10 group leaders will each deliver the program to 5-9 groups of students.

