**Method:**

The effectiveness of OVK will be tested in a randomized controlled trial with two conditions, intervention (OVK) and control condition (care as usual). Schools are randomly assigned to research conditions. OVK will be incorporated in the school curriculum, maximizing program attendance. OVK consists of 16 lessons of 50 min, given by trained psychologists to groups of 11-15 students. OVK contains Cognitive Behavioral Therapy, social skills training, problem solving and decision making. Outcomes are measured at 6, 12, 18 and 24 months follow up, to monitor long term program effects. Primary outcome is level of depressive symptoms, secondary outcomes are: anxiety, hopelessness, cognitive bias, substance use, truancy, life satisfaction, coping, self-efficacy, optimism, happiness, friendship, school performance and school attitude. The questionnaires for students will be administered in the school setting. Parents will complete a questionnaire at baseline only.

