**Figure 1 F1:**
[figure not shown]
**Study design**.

To test the (long term) effectiveness of the program, the outcomes will be assessed through self-report questionnaires approximately 1 month before the start of the program (baseline: T1), directly after the program (T2), and 6 (T3), 12 (T4), 18 (T5) and 24 (T6) months after the end of the program. Adolescents in the control condition will complete the questionnaires at exactly the same time points. Parental self-reports will be administered at baseline only. Adolescents assigned to the experimental condition will receive the OVK program, and adolescents in the control condition will receive care as usual (no program). As a reward for participation in the study, the schools in the control condition will receive a training for teachers in the OVK program between T3 and T4, on the strict condition that they will not provide the program to the adolescents who participated in the study.

OVK will be incorporated into the school curriculum; the 16-lesson program will be delivered once a week by trained psychologists to groups with a maximum of 15 adolescents. Incorporating the program in the school curriculum enables us to truly provide the program to all adolescents in a certain grade. As a result, high attendance rates will be assured and no stigmatization will occur. To keep the attrition rates at a minimum, all adolescents absent at a given measurement will be provided another possibility in the same time period to complete the questionnaire. Also, adolescents who leave school will be asked, with assistance of the school, to continue participating in the study. The trial is registered at the Dutch Trial Register: NTR2879.

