### Data analysis

Data will be analyzed in accordance with the intent-to-treat principle and for the completers only. Multiple imputations will be used for missing observations at follow-ups. The hypotheses will be tested with regression analyses for dichotomous outcome measures in MPLUS 5.1 [65,66]. Additional analyses will be conducted to test effects of the intervention on development of depressive symptoms using latent growth curve (LGC) modeling [66], in which the intercept and slope of levels of depressive symptoms using scale scores (as we will have 6 assessments) are modelled, and effects of condition can be examined. We will check for possible baseline differences between the two conditions in demographic variables (e.g. age, gender, school level, and ethnic background) and depressive symptoms. Moreover, variables that show different distributions between the two groups will be entered as confounders in all models testing the effectiveness of the program. The cluster effect-students were 'nested' in classes-will be handled by getting robust variance related estimates based on the first order Taylor series linearization method using Stata's procedures for design based analyses [65]. Reporting of the results of the study will be in accordance with the CONSORT statement [67].

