### Strengths and limitations

Several strengths of the present study are identified. First, both prevention of aversive outcomes and the promotion of positive development are central in OVK. Therefore, program effects on depression, anxiety, and hopelessness, but also on optimism, happiness and life-satisfaction will be examined. Second, program effects will be tested in randomized controlled study and a large sample. Third, trained psychologists will administer the program [22,23]. Fourth, during OVK adolescents learn Cognitive Behavioral Therapy principles, which have been shown to be effective in treating depression in adults and adolescents [26,27]. Fifth, OVK is based on an effective universal depression prevention program [28]. Moreover, the program will be incorporated in the regular school curriculum, enabling all adolescents to participate in the program, maximizing high program attendance and minimizing measurement attrition rates.

Limitations of the present study are present as well. No placebo treatment will be included in the design, limiting the extent to which lower depressive symptoms in the intervention condition can be uniquely ascribed to the program. Another limitation of the study will be the single use of self-reports; interviews by trained professionals would be more sensitive in identifying depressive symptoms [68]. At the other hand, depressive symptoms can be measured reliably and validly by means of self-reports [43,44], and program effect sizes were not related to assessment mode [23]. Because of financial constraints, no integrity check performed by others than group leaders themselves will be conducted. Group leaders will fill out program adherence forms, enabling us to check which parts of each lesson were not covered and why.

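### The robust variance clusters on class only, although ten leaders each teach across several intervention classes; if leaders differ, the interval for a general programme effect is somewhat too narrow

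*Protocol article*

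**What the plan says.** On delivery, the Program delivery section states "The 10 group leaders will each deliver the program to 5-9 groups of students" and "Classes will be split up in two groups, thus consisting of 12-15 students". The section on program content gives leaders an active part: "Group leaders are responsible for group atmosphere and cohesion, and they will guide discussions and role-plays". The Design section says that control pupils get no programme, so leaders exist in one arm only.

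On allocation, the abstract states "Schools are randomly assigned to research conditions".

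On the analysis, the Data analysis section fixes both the cluster level and the estimator. For the level it says "The cluster effect-students were 'nested' in classes-will be handled by getting robust variance related estimates". The estimator it names is a design-based variance from Taylor linearisation. The sample-size paragraph under Participants and procedure allows for clustering in schools. Leader appears in neither place.

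**The concern.** A variance estimator clustered on class allows for any correlation within a class and assumes none between classes. In the intervention arm, classes taught by the same leader share whatever that leader adds or takes away. This part of the uncertainty is averaged over ten leaders, but the stated method averages it over the number of classes. The arms are also asymmetric, because there is no matching term in the control arm.

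What is at stake is the width of the interval for the programme effect when it is read as applying to schools and leaders in general. Implications for practice reads it that way, since it speaks of implementing the programme in schools. Because the document states the cluster level outright, this is a choice it has made and not a detail left to an analysis plan.

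**Working it through.** **The plan's own figure.** For a standardised effect of 0.20, two-sided alpha of 0.05 (sidedness is not stated; two-sided is assumed) and power of 0.80, the simple two-mean formula gives 393 per arm. Allowing for 20% attrition, 393/0.80 = 491.25, rounded up to 492. Reaching 662 needs a further factor of 662/492 = 1.35 for clustering and imputation. The document gives no ICC, cluster size or imputation loss, so 662 can be neither confirmed nor refuted. No part of it is attributed to leaders.

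**Inputs from the document**
- 10 leaders with 5 to 9 groups each, so 50 to 90 groups.
- Two groups of 12 to 15 per class, so classes of 24 to 30 and 5/2 = 2.5 to 9/2 = 4.5 class equivalents per leader.
- 662 pupils per arm.

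**Assumptions**
- 25 classes per arm. This is 50 groups / 2, the low end; 662/25 = 26.5 pupils per class fits the stated sizes.
- Class ICC (C) of 0.02.
- Leader ICC (L) of 0, 0.01, 0.02 or 0.05.
- Continuous outcome with total SD 1.

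**Formulas**
- Residual term: e = (1 − L − C)/662.
- Control arm variance: C/25 + e.
- Intervention arm variance with leaders as a random sample: L/10 + C/25 + e.
- Intervention arm variance as the class-based method counts it: L/10 is replaced by L/25 if both halves of a class share a leader, or by L/50 if they have different leaders.
- Coverage of a nominal 95% interval: 2Φ(1.96 × SE ratio) − 1.

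**Example, L = 0.02, shared leader.** e = 0.96/662 = 0.00145. Full variance = (0.00200 + 0.00080 + 0.00145) + (0.00080 + 0.00145) = 0.00650, SE 0.0806. Counted variance = (0.00080 + 0.00080 + 0.00145) + 0.00225 = 0.00530, SE 0.0728. Ratio 0.903.

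| Leader ICC | Between-leader SD | Full SE | Class-based SE (shared / different leaders) | SE ratio | Coverage |
|---|---|---|---|---|---|
| 0 | 0 | 0.068 | 0.068 / 0.068 | 1.000 / 1.000 | 95.0% / 95.0% |
| 0.01 | 0.10 | 0.074 | 0.070 / 0.069 | 0.944 / 0.925 | 93.6% / 93.0% |
| 0.02 | 0.14 | 0.081 | 0.073 / 0.070 | 0.903 / 0.868 | 92.3% / 91.1% |
| 0.05 | 0.22 | 0.097 | 0.080 / 0.074 | 0.825 / 0.758 | 89.4% / 86.3% |

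A simulation of 4,000 runs per setting agreed broadly. Non-coverage was 4.8% to 4.9% at leader ICC 0, 6.6% to 6.8% at 0.01 and about 8.6% at 0.02.

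The 0.05 row is an extreme case: a between-leader SD of 0.22 exceeds the whole planning effect of 0.20.

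**The case against.** The strongest objections concern size and separateness, and most of them stand.

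- **False-positive rate.** A reader might infer from the table that a useless programme would be declared effective more than 5% of the time. The document does not support that. Control pupils have no leader, so leader variance here is variation in the programme's effect. If the programme affects nobody, that variance is zero. Extra false positives would need leaders whose effects differ yet average exactly zero. What stands is a statement about interval width.
- **Fixed leaders.** If inference is confined to these ten leaders, the term drops out. That is a recognised position, but the document does not adopt it and points to wider use.
- **Leaders may differ little.** Program delivery describes MSc-level leaders, a common five-day training and supervision, all of which work against large differences. This is fair, and it is why 0.01 to 0.02 is the working range.
- **Overlap with school clustering.** School is the randomised unit. If each leader works in one school, clustering on school absorbs the leader effect and nothing separate remains. The document does not say how leaders are spread over schools.
- **Ten leaders against 50 to 90 groups.** That contrast would overstate the loss. The stated method clusters on classes, about 25 here, and already captures leader correlation within a class.
- **Fidelity and record keeping.** The limitation "no integrity check performed by others than group leaders themselves will be conducted" is disclosed and has no bearing on the standard error. Nothing shows that leader identity goes unrecorded.
- **Scale.** The first-named analysis is regression for dichotomous outcomes. The figures above are on a continuous scale and do not quantify that test.

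**Conclusion.** The point holds in conditional form. The cluster level stated in Data analysis does not match the delivery structure stated in Program delivery. If leaders differ in effect and the result is to apply beyond these ten, the interval is too narrow.

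For a leader ICC of 0.01 to 0.02, the shortfall in the standard error is about 6% to 13%, and coverage is about 91% to 94% instead of 95%. These figures rest on assumed ICCs, 25 classes and 662 analysed per arm, and they compare leader with class clustering. The shortfall that would remain after clustering on school cannot be calculated, because the number of schools and the leaders' allocation to them are not given.

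Severity is low. The cluster level itself, class instead of the randomised school, is the larger matter, and this point belongs beside it.

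**What to change.** In the clustering sentence of Data analysis, make school the cluster level. This matches the unit of randomisation and also absorbs leader effects if each leader works in a single school.

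Where a leader serves more than one school, add a partially nested model alongside the school level. It has a leader random effect in the intervention arm and none in the control arm, with small-sample degrees of freedom because there are only ten leaders and, as the Design section notes, few schools. State it at least as a sensitivity analysis, and report the between-leader variance with the result.

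The cost is one or two sentences and a modest amount of extra analysis. The downside is somewhat wider intervals and a leader variance estimated imprecisely from ten leaders.

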### Measures

The primary outcome will be the level of depressive symptoms at 6, 12, 18 and 24 months follow up measured with the Child Depression Inventory (CDI) [42], which is reliable and valid [43,44]. Possible mediators will be coping, cognitive bias, self-efficacy, hopelessness and optimism. The Children's Coping Strategies Checklist Revision 1 [45] will be used to assess coping styles. Cognitive bias will be measured with a questionnaire specifically developed to assess the cognitive biases addressed in OVK [46]. Self-efficacy will be assessed with the Self-Efficacy Questionnaire for Children SEQ-C [47], which has satisfactory internal consistency and good validity. Hopelessness will be measured with Beck's Hopelessness Scale (BHS) which has good reliability and validity [48]. Optimism will be measured with LOT-R which has good validity and reliability properties [49].

The 'negative' secondary outcomes will be the level of anxiety, truancy and substance use. Anxiety will be assessed with the Revised Children's Manifest Anxiety Scale (RCMAS) [50]. The RCMAS is a widely used questionnaire that assesses anxiety symptoms in children and adolescents. This scale has demonstrated good reliability and correlates with other measures of anxiety symptoms. Truancy will be measured through a self-report question: 'How many hours did you skip school the past 4 weeks?'. Widely used standard instruments will be administered to tap the frequency and intensity of alcohol [51,52] and tobacco use [53,54]. Positive secondary outcomes are life satisfaction, happiness, school grades and attitude, and participation in friendship groups. Life satisfaction will be measured with the Students Life Satisfaction Scale [55]. The SLSS assessed adolescents' global satisfaction or contentment. Studies have found the SLSS to have good internal consistency and test-retest reliability and to correlate highly with other subjective well-being measures [55]. Happiness will be measured with the Cantril Ladder [56]. Academic performance will be assessed by asking adolescents to list their last grades on core subjects. Clique membership and friendships will be measured with one sociometric item: "Who are your best friends?". Information on socio-demographic factors, for example, age, sex, ethnicity, religious affiliation, and educational level, will also be obtained.

### Parent measures

The parent questionnaire will include measures of socio-demographics of both parents and the participating child: Information about (prior) diagnosis and treatment, marital status, parental SES indicators such as education, employment, working hours, and salary. In addition, parents' own characteristics and parenting skills will be included (depressive symptoms, optimism, general parenting and mindful parenting). All instruments are widely used and have satisfactory psychometric properties. The Beck Depression Inventory [57] will be used to assess symptoms of depression. Anxiety will be tapped by the trait scale of STAI-DY; a Dutch version of the Spielberger State Trait Anxiety Inventory [58,59]. Optimism will be measured with the LOT-R [49]. General parenting, including responsiveness, and psychological and behavioral control, will be measured with the Dutch versions of the Acceptance-Rejection scale from the Child Report of Parent Behaviors Scale [60], 'Psychological Control' Scale-Youth Self-Report (PCS-YSR) [61], and the 'Parent Regulation Scale'-Youth Self-Report (PCS-YSR) [62], respectively. Parental autonomy support will be tapped with an adapted version of the Autonomy Support Scale [62,63]. Mindful parenting is assessed with the Dutch version of the Interpersonal Mindfulness Parenting Scale IM-P [64].

### Data analysis

Data will be analyzed in accordance with the intent-to-treat principle and for the completers only. Multiple imputations will be used for missing observations at follow-ups. The hypotheses will be tested with regression analyses for dichotomous outcome measures in MPLUS 5.1 [65,66]. Additional analyses will be conducted to test effects of the intervention on development of depressive symptoms using latent growth curve (LGC) modeling [66], in which the intercept and slope of levels of depressive symptoms using scale scores (as we will have 6 assessments) are modelled, and effects of condition can be examined. We will check for possible baseline differences between the two conditions in demographic variables (e.g. age, gender, school level, and ethnic background) and depressive symptoms. Moreover, variables that show different distributions between the two groups will be entered as confounders in all models testing the effectiveness of the program. The cluster effect-students were 'nested' in classes-will be handled by getting robust variance related estimates based on the first order Taylor series linearization method using Stata's procedures for design based analyses [65]. Reporting of the results of the study will be in accordance with the CONSORT statement [67].

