### Participants and procedure

Participants will be adolescents in their second year of secondary school (8th grade, ages 12-14) [28]. Secondary schools in the southern and middle part of the Netherlands will be approached to participate in the study. Only adolescents in middle school grade 8 will be included. We will ensure inclusion of low SES and ethnic minority groups, as well as different educational levels (Dutch middle school prepares adolescents for vocational up to university level). The exclusion criterion consists of parental refusal of their child's participation in the study. When schools show interest, they will be asked to participate with as many as possible second grade classrooms. We expect that-once included in the study-across the entire study period, approximately 80% of adolescents will provide complete data [33,34].

A meta-analysis on 17 controlled studies on PRP indicated the significant average effect size to be 0.20 at 12-months follow-up with the CDI > 13 score as cut-off [28]. Power analysis (G-power) based on this 12-month mean effect size takes into account a maximum of 20% attrition over time, as well as clustering of data in schools and loss of power due to multiple imputation. Based on this power analysis, sample sizes need to be 662 adolescents per condition (alpha < .05, power = .80); at least 1,324 adolescents will be included.

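### The primary outcome is a level of CDI symptoms, the main test is for dichotomous outcomes, and the 0.20 used for sizing has no stated metric

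*Protocol article*

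**What the plan says.** All references are to the Protocol article.

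- **Measures:** "The primary outcome will be the level of depressive symptoms at 6, 12, 18 and 24 months follow up", measured with the CDI. No cut-off or dichotomised version of the CDI is defined there.
- **Goals and hypotheses, and Discussion:** the hypothesis is that the programme limits the rise in symptoms over 24 months, and that intervention pupils show fewer symptoms at follow-up than controls.
- **Data analysis, main test:** "The hypotheses will be tested with regression analyses for dichotomous outcome measures in MPLUS 5.1". No cut-off is named here either.
- **Data analysis, second model:** "Additional analyses will be conducted to test effects of the intervention on development of depressive symptoms using latent growth curve (LGC) modeling". This model uses scale scores from the six assessments and examines the effect of condition on intercept and slope.
- **Participants and procedure:** the sizing takes from a meta-analysis of the parent programme an "average effect size to be 0.20 at 12-months follow-up with the CDI > 13 score as cut-off". From this, "sample sizes need to be 662 adolescents per condition" ("alpha < .05, power = .80"), after allowing for 20% attrition, clustering in schools and multiple imputation.

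**The concern.** Three elements that should describe one quantity do not. The outcome is a level, the hypothesis is a change in that level, and the test that carries the hypotheses is for a yes/no outcome. The analysis on the matching scale is planned but ranked second.

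Two things are at stake. First, the plan contains two candidate main results, a difference in the proportion above some cut-off and a difference in scale-score trajectory. They can disagree, and the text supports calling either one confirmatory, which leaves room to choose after the data are seen. Second, dichotomising a score discards information. If the 0.20 is a mean difference in SD units, the sample size supports the analysis ranked second and not the one ranked first.

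**Working it through.** **1. The plan's own figure.** Inputs from Participants and procedure: effect 0.20, alpha 0.05 (two-sided assumed, as sidedness is not given), power 0.80, attrition 20%, 662 per arm.

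- Two means: n = 2(1.960 + 0.842)² / 0.20² = 393 per arm.
- Attrition: 393 / 0.80 = 492 per arm (rounded up).
- Remaining factor to reach 662: 662 × 0.80 / 393 = 1.35, to be shared between clustering and imputation.

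The article does not itemise that factor, so 662 can be neither confirmed nor refuted. If 0.20 is a standardised mean difference and 662 does give 80% power, the effective size is about 393 per arm (power 80.1%).

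**2. Reading A: 0.20 is a standardised mean difference on the CDI score.** Assumptions made here and not in the document: a normal score, and control proportions above the cut-off between 10.0% and 24.5%. The Background gives those two figures as the shares with depressive symptoms at ages 11 and 15.

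- Intervention proportion: p_I = 1 − Φ(z + 0.20), where z = Φ⁻¹(1 − p_C).
- At 10.0%: z = 1.282, p_I = 1 − Φ(1.482) = 6.9%.
- At 24.5%: z = 0.690, p_I = 1 − Φ(0.890) = 18.7%.
- Power = Φ{[√n·|p_C − p_I| − 1.96·√(2p̄(1 − p̄))] / √[p_C(1 − p_C) + p_I(1 − p_I)]}.
- At 10.0%, n = 393: (0.611 − 0.771) / 0.393 = −0.41, so power is 34%.
- At 24.5%, n = 393: (1.156 − 1.140) / 0.580 = 0.03, so power is 51%.

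| Control rate | p_I | Power, 393/arm | Power, 530/arm | Effective n/arm for 80% |
|---|---|---|---|---|
| 10.0% | 6.9% | 34% | 44% | 1,284 |
| 15% | 10.8% | 42% | 53% | 1,007 |
| 20% | 14.9% | 47% | 59% | 861 |
| 24.5% | 18.7% | 51% | 64% | 780 |
| 30% | 23.4% | 55% | 68% | 714 |

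The 530 column takes off only the 20% attrition (662 × 0.80 = 529.6) and allows nothing for clustering or imputation. With a median split (control rate 50%), the most favourable cut, power at 393 per arm is 61%.

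**3. Reading B: 0.20 is already an effect on the binary outcome, as Cohen's h.**

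- p_I = sin²(arcsin√p_C − 0.10).
- 10.0% falls to 4.8%: power at 393 per arm is 79%.
- 24.5% falls to 16.5%: power at 393 per arm is 80%.
- On a normal score these reductions correspond to shifts of about 0.38 SD and 0.29 SD.

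A standardised risk difference of 0.20 also gives about 80%.

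**4. Reading C: 0.20 is a d converted from an odds ratio.** OR = exp(0.20·π/√3) = 1.44. Power at 393 per arm is 29% at a control rate of 10.0% and 55% at 24.5%.

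**5. The passages side by side.** Under A or C the dichotomous test falls well short of 80%. Under B the power is kept, but the sample size describes a proportion above a cut-off, which Measures does not name as primary. No reading makes outcome, main test and sizing agree.

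**The case against.** A reader might infer that the trial's power is in fact 34% to 51%. The document does not support that as a plain statement, for three reasons.

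- The sizing text attaches 0.20 to a cut-off and gives no metric. The binary reading is open, and under it nothing is lost.
- The 10.0% and 24.5% are background shares with symptoms, not rates of CDI > 13. Pupils are 12 to 14 at entry and followed for two years after the programme, so age 11 lies outside the trial and the 34% end is the less relevant one.
- The 393 is back-solved from 80% power, because the allowances behind 662 are not itemised.

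These points stand. They make the power figure conditional but do not remove the mismatch.

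A reader might also infer that anxiety, life satisfaction and happiness will all be dichotomised, since the sentence covers the hypotheses without exception. That rests on one compressed sentence in an article. No cut-offs for those scales appear, and the sentence could mean only that this method serves whichever measures are dichotomous. I do not press it. Nor do I press that pupils already above a cut-off at baseline would be kept in a binary analysis, because the article is silent on it.

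Finally, the growth model is already planned, so the hypothesis about increase would be tested. That is correct: the defect lies in its rank and in the sizing, not in its absence. Declaring a defined CDI cut-off endpoint primary would also reconcile the passages, provided it were sized from stated event rates.

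**Conclusion.** The point holds as an inconsistency that should be resolved before analysis. Outcome and hypothesis are on the scale score, the main test is for dichotomous outcomes, the matching model is only additional, and the metric of the 0.20 is not given. This part needs no assumption.

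The consequence for power is conditional. If 0.20 is a scale-score standardised mean difference, the dichotomous test has about 34% to 51% power instead of 80% (two-sided 0.05, normal score, about 393 effective per arm, control rates of 10.0% to 24.5% above the cut-off), or 44% to 64% at 530 per arm. To reach 80% it would need 2.0 to 3.3 times the effective sample (780/393 to 1,284/393). If 0.20 is a binary effect such as Cohen's h, about 80% is kept and the fault is that the sizing belongs to an endpoint not named as primary. The article does not show which reading applies.

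**What to change.** 1. Make the planned scale-score CDI model the confirmatory analysis, either as the growth model or as a baseline-adjusted model that accounts for clustering, and name the condition effect that is the test.
2. Label the CDI cut-off regression secondary, and state its cut-off.
3. State the metric of the 0.20. It should not simply be relabelled a standardised mean difference, because the article does not show that it is one. If the metric does not match the confirmatory analysis, restate the power for that analysis.

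The cost is small for the first two steps: they reorder analyses already planned and need no new data. The third costs a check of the source and possibly a new power statement. The downside is that the headline result becomes a difference in means or slopes, which is less immediate for schools than a proportion, but the proportion is still reported.
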